##### Feasibility of Launch Components

To assess the feasibility of parents’ abilities to deliver CM-EA to their emerging adult children, a parent coach session checklist will be developed. The checklist will be completed at the end of each session. Here, the parent coach will report on what CM-EA components the parents reported attempting since the last session (eg, creating a reward menu with the emerging adult, providing rewards, or discussing self-management plans for poly-SU triggers).

The statistical analyses will focus on parents’ delivery of CM-EA components to their emerging adult children. The models will be formulated as described for aim 1, with repeated measurements of parent adherence to CM-EA (level 1) nested within families (level 2) [93]. An initial unconditional model will be used to estimate the proportion of variance in CM-EA delivery that is attributable to sessions and parents. This will be followed by a model to estimate the initial level and rate of change in CM-EA adherence. Of note, if the initial measurement models indicate that scoring should occur for the course of *Launch* (ie, at the level of parents) rather than session by session, the descriptive parent-level average scores will be evaluated relative to predefined thresholds for acceptable delivery of CM-EA components. The adherence models will be used to determine whether parent coaching of CM-EA leads to actual implementation of CM-EA in the participating families’ households. Any trends observed in the data will be incorporated into the qualitative interviews detailed in the following sections (eg, select CM-EA components not being implemented at high levels).

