### Intervention

#### CM-EA Coaching

Parents in either CM-EA condition (parent CM-EA component only or parent CM-EA plus in-person PRSS for the emerging adults) will be virtually coached to deliver CM-EA by an at least Bachelor’s-level paraprofessional via web-based videoconferencing. Weekly CM-EA coaching sessions are expected to last 20 to 40 minutes each. This service was developed by the research team and collaborators. Strategies are well specified, and multiple tools (session checklists and worksheets) facilitate CM-EA delivery. CM-EA draws from CM approaches that target poly-SU in adults and teenagers. CM-EA is grounded in a family-based CM model that uses both behavior modification and cognitive behavioral strategies. CM has garnered tremendous support in the SU treatment field, and our team has modified and examined CM specifically for emerging adults. All components involve a support person, which in *Launch* is a parent (see the aforementioned definition of “parent”). After introducing CM-EA, a contingency contract is developed (described in the following paragraph) that provides emerging adults with rewards for negative drug screens and completion of developmentally appropriate goals that build recovery capital (eg, submitting job applications and opening a bank account), along with disincentives for positive screens or engaging in inappropriate behaviors (eg, using the parent’s car without permission). Concurrently, parents are taught to conduct random urine drug screens (instant). In addition, parents are trained to complete functional analyses that identify the emerging adult’s poly-SU triggers. Triggers are targeted via self-management planning and drug refusal skill training tailored to each emerging adult. Before ending, plans will be made with the family to sustain recovery and improvements in other behaviors.

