After recruitment, interested participants will meet with a research team member to complete informed consent. Then, emerging adults will complete an approximately 1-hour virtual baseline interview. On the basis of the experience of the research team, 1-hour assessments rarely present a significant response burden, but the research team will use breaks to attenuate circumstances that threaten the validity of the assessments. A stratified permuted block randomization design [80] will be used to randomize the families to one of three treatment conditions: (1) web-based CM-EA parent coaching only, (2) in-person PRSS for the emerging adult only, or (3) both web-based CM-EA parent coaching and in-person PRSS for the emerging adult. Families will receive *Launch* services for approximately 5 months. All activities with the parents will be web-based, assessments with emerging adults will be web-based, and PRSS sessions with the emerging adults will be in person. The parent coach and peer workers will track session attendance. At 6 months after the baseline, emerging adults will complete a virtual, 1-hour follow-up assessment, and parents will complete an approximately 1-hour qualitative interview (see the *Measures* section) that will also include a limited number of brief quantitative questionnaires. At the end of their participation in the project, the parent coach and peer workers will complete an approximately 1-hour qualitative interview about *Launch* services (see the *Measures* section).

#### Aim 3

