#### Peer Worker and Parent CM-EA Coach Measures

Peer workers delivering PRSS and the parent CM-EA coach will complete checklists of services delivered after each session and will engage in a follow-up qualitative interview at the end of their participation in the project. The peer workers will complete a checklist after each session to indicate which topics they covered with their emerging adult client. The CM-EA parent coach will complete a checklist after each session with each parent noting each CM-EA skill that the parent indicated using since the last time they met with the coach. Qualitative interviews with both types of participants will delve deeper into implementation-related concepts, perceived or actual impacts on emerging adults or parents, and other suggestions for service improvement.

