### Analysis Plan

#### Aim 1

Aim 1 includes 2 groups of analyses. The first group is a preliminary psychometric evaluation of the adapted instruments measuring the adherence of (1) coaches training parents in the use of CM-EA and (2) standard PRSS plus vocational or educational skill building. The number of families is modest, but each will have numerous repeated measurements. The second group of analyses will determine whether coaches can train parents to deliver CM-EA and whether peer workers can deliver the combined services (ie, PRSS plus vocational or educational skill building). All data will be nested, with repeated measurements (level 1) nested within families (level 2), but the actual number of measurements will vary for each family and type of adherence. Nesting will be addressed using mixed-effects regression models. To evaluate parent training, the model will include a linear time term, which will estimate the initial level of coach adherence and test for change over time, and this will be interpreted relative to theory-based standards for acceptable training. To evaluate the delivery of PRSS plus vocational or educational skill building services, the same type of model will be performed. Combined, the results will determine whether the proposed protocols lead to the expected levels of adherence for coaches as well as peer workers, and low adherence scores will be investigated during the proposed qualitative interviews.

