##### Acceptability of Launch Components

Descriptive data analyses will assess the average number of sessions attended, cancelled, no-showed, and rescheduled for parents with the parent coach and for emerging adults with PRSS. Similarly, data analyses will assess the average and item-level client satisfaction ratings of parents and emerging adults with *Launch* services. The attendance and CSQ-8 scores will be used to determine the acceptability of *Launch* services. Themes from the qualitative interviews will aid in the interpretation of the quantitative data.

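### The parent-delivery checklist covers a window that lengthens with every missed session, and the described model has no term for its length, so delivery is confounded with session spacing

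*Protocol article*

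**What the plan says.** The recall window is defined twice, both times by the previous meeting and not by a number of days. In the Analysis Plan (Aim 2, Feasibility of Launch Components), "the parent coach will report on what CM-EA components the parents reported attempting since the last session". In the Measures section (Peer Worker and Parent CM-EA Coach Measures), the coach completes the checklist "noting each CM-EA skill that the parent indicated using since the last time they met with the coach".

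A score exists only for a session that took place: "The checklist will be completed at the end of each session".

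The planned interval is a week. CM-EA Coaching states "Weekly CM-EA coaching sessions are expected to last 20 to 40 minutes each", and the Aim 2 part of the Protocol section has families receiving "services for approximately 5 months". Irregular spacing is foreseen. The Aim 1 analysis expects that "the actual number of measurements will vary for each family and type of adherence", and Acceptability of Launch Components will summarise the "average number of sessions attended, cancelled, no-showed, and rescheduled for parents with the parent coach". Those counts are assigned to acceptability.

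The delivery model follows the Aim 1 form: repeated measurements within families, first an unconditional model, then an initial level and a rate of change. No interval term is named. If scoring turns out to belong at parent level, parent averages are compared with predefined thresholds. The result is meant to show whether coaching leads to CM-EA being carried out at home.

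**The concern.** Noting each skill used since the last meeting reads most naturally as a used-or-not-used record. Such an item is more likely to be ticked over three weeks than over one, even if the parent behaves identically each week. A missed session therefore has two effects. It removes one measurement, and it lengthens the exposure behind the next one. This point concerns only the second.

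At stake is the main quantitative evidence on whether parents deliver CM-EA. Two parents with the same weekly use can receive different scores because one was seen less often. If spacing changes over the programme, part of the estimated slope reflects spacing and not delivery.

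**Working it through.** The article gives no figure to reproduce on this point: no checklist rate, attendance rate or expected slope. Every rate below is an assumption.

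**Inputs from the article.** Weekly sessions; about 5 months of services (5 × 52/12 ≈ 22 weeks); a window that runs from the previous session; a linear-time model with nesting in families. There are 48 families over three conditions, two of which include coaching. With equal allocation (assumed, as the ratio is not stated) that is 48 × 2/3 = 32 coached families.

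**1. One checklist.** With weekly use probability p, independent weeks and a window of k weeks, P(ticked) = 1 − (1 − p)^k.

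| p | 1 week | 2 weeks | 3 weeks |
|---|---|---|---|
| 0.30 | 0.30 | 1 − 0.70² = 0.51 | 1 − 0.70³ = 0.66 |
| 0.50 | 0.50 | 0.75 | 0.88 |
| 0.90 | 0.90 | 0.99 | 1.00 |

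Near the ceiling little room for bias remains.

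**2. Average per attended session.** If each weekly session is attended at random with probability a, the long-run mean score is 1 − Σ a(1 − a)^(k−1)(1 − p)^k = p / [p + a(1 − p)].

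| p | a = 1 | a = 0.75 | a = 0.50 |
|---|---|---|---|
| 0.30 | 0.30 | 0.30/0.825 = 0.36 | 0.30/0.65 = 0.46 |
| 0.40 | 0.40 | 0.40/0.85 = 0.47 | 0.40/0.70 = 0.57 |

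**3. Break-even.** A parent seen every 2 weeks scores the same as a weekly attender with p = 0.50 if the true weekly use is 1 − 0.50^(1/2) = 0.29.

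**4. Trend.** Simulation: 100 runs, 32 families, 22 weeks, 8 yes/no components, a random family effect, and a linear-time mixed model with a family intercept. Attendance was assumed to fall from 0.95 to 0.40.

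| True weekly delivery | Fitted, window since last session | Fitted, fixed 7-day window |
|---|---|---|
| constant 0.40 | 0.40 to 0.59 (significant rise in 100 of 100 runs) | 0.40 to 0.41 |
| 0.40 to 0.25 | 0.41 to 0.44 | 0.41 to 0.26 |
| 0.40 to 0.15 | 0.41 to 0.31 | not run |

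With full attendance and constant delivery the fitted score stayed at about 0.41 throughout, so the artefact comes from spacing.

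**5. Variation between parents.** If p follows a Beta(0.6, 1.4) distribution (mean 0.30, assumed), the mean of (1 − p)² is (1.4 × 2.4)/(2 × 3) = 0.56, and the mean of (1 − p)³ is 0.56 × 3.4/4 = 0.476. The 2- and 3-week readings become 0.44 and 0.52 instead of 0.51 and 0.66. The inflation is smaller but still present.

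**6. Does an offset remove it?** Under the model in step 1, −ln(1 − P) = k × [−ln(1 − p)]. At p = 0.30 this is 0.357, 0.713 and 1.070 for 1, 2 and 3 weeks, proportional to k. A complementary log-log link with log(interval) as offset therefore returns the weekly rate.

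**The case against.** A reader might infer that parents who attend less will get higher scores and that falling attendance will look like improving delivery. The article does not support so firm a statement. It needs roughly equal weekly use in good and poor attenders, recurring yes/no items, and attendance that declines. The article states none of these. If poor attenders also deliver much less, their scores can still be lower: the simulated fall from 0.40 to 0.15 still appeared as a fall, though an understated one.

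Other counter-arguments have force:
- The checklist is still to be developed, and the article does not say whether items are yes/no, counts, or scored against the components due.
- A session rescheduled within the week adds no long window.
- Poor recall over a long gap would pull the other way.
- If a component is credited once over the whole course, adjoining windows together cover the same period up to the last session held, and the bias largely disappears.
- Some components, such as drawing up a reward menu, are done once. The formula in step 1 does not describe them, and a 7-day-only question would lose any completed earlier in a gap.

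It can also be said that covariates belong in an analysis plan that is not shown. That is fair for the model term. It does not answer the recall window, which the article itself fixes in two sections, and an interval can be modelled later only if it has been recorded. The article says that session attendance is tracked. It does not say that session dates are, so they should not be assumed to be available.

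**Conclusion.** The concern holds in a bounded form. By definition the checklist window lengthens when a weekly session is missed, and the described model treats all checklists alike. For recurring components noted as used or not used, this overstates delivery after longer gaps at equal weekly use. If attendance falls, it can mask a decline or create an apparent rise. A parent-level average of session scores set against thresholds carries the same inflation.

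Under independent weeks at weekly use 0.30, the score is about 0.36 at 75% attendance and 0.46 at 50%, against 0.30 at full attendance. These figures are illustrations and not predictions. The effect is smaller with variation between parents, week-to-week persistence, prompt rescheduling or use near the ceiling. What is established is the direction of the pull at equal weekly use. The ranking of good and poor attenders, and the sign of the observed slope, are not.

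**What to change.** 1. Keep the question about the time since the last session, so that one-off components completed during a gap are still credited.
2. Record the session date, and hence the days since the previous session, on the checklist.
3. For recurring components, include the interval in the delivery model. Either use a complementary log-log link with log(days/7) as offset, which gives a weekly rate if use is roughly constant within the gap, or use the interval as a covariate where that assumption is doubtful.
4. Score one-off components as completed or not over the course. Averaged per session, one completion counts 1/20 over 20 sessions but 1/10 over 10.
5. Optionally add a tick for use in the past 7 days, for recurring components only.
6. Report delivery alongside attendance.

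The cost is one extra field on a checklist that is still to be developed and one extra model term.

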##### Acceptability of Launch Components

Descriptive data analyses will assess the average number of sessions attended, cancelled, no-showed, and rescheduled for parents with the parent coach and for emerging adults with PRSS. Similarly, data analyses will assess the average and item-level client satisfaction ratings of parents and emerging adults with *Launch* services. The attendance and CSQ-8 scores will be used to determine the acceptability of *Launch* services. Themes from the qualitative interviews will aid in the interpretation of the quantitative data.

##### Secondary Outcomes

While we will not have sufficient power to perform any statistical analyses of secondary outcomes (eg, SU and self-efficacy), descriptive statistics of all emerging adult secondary outcomes will be reported to aid in power analyses for a future large-scale study of *Launch*.

##### Qualitative Data Analysis

All interviews will be digitally taped and then transcribed verbatim and deidentified. The deidentified transcripts will then be uploaded to the most updated version of Dedoose (SocioCultural Research Consultants) [94] for qualitative analyses using inductive coding [95]. One member of the research team will perform an initial round of open coding of the transcripts, followed by coding common themes that emerge across transcripts using axial and pattern coding [95]. This coding pattern will then be reviewed by 1 to 2 other research team members to iteratively interpret the coded data. Finally, research team members involved in coding will review a summary of the qualitative findings to reach a consensus on their accuracy. These findings will be used to further adapt and improve the *Launch* service package via an iterative process from the perspectives of the parent coach, peer workers, and participating emerging adults and parents.

#### Aim 3

The payer and provider interviews are less open ended than the interviews of other participants; thus, some responses will produce lists rather than thematic findings (eg, lists of potential outcomes of interest). However, when appropriate, the qualitative methods described for aim 2 will be used to analyze the interview data with payers and providers.

#### Sample Size and Power Considerations

Because this study is *developmental work*, the sample size (n=48 families) was driven by appropriateness for pilot study objectives rather than by statistical power computations for formal hypothesis testing [96,97]. Pilot studies play an important role in providing information for the planning and justification of future large-scale trials (eg, for feasibility of service protocols and refinement of recruitment and assessment strategies) [98]. The sample size conforms to guidelines for pilot studies (n≥12 per group) [99,100] and provides representativeness of a diversity of participant characteristics for examining feasibility, data collection procedures, and *Launch* service acceptability. However, this pilot will inform power analyses and sample size planning for a subsequent larger effectiveness trial. Because of this, it is important for the measurement and research design to support accurate estimates of the focal model parameters—thus, there are important considerations regarding the precision of estimated effects. For the measurement models proposed, the sample is sufficient for stable and precise estimates of family and item parameters and SEs. Specifically, sample sizes in the range of 16 to 36 are sufficient for 95% confidence that the estimated person or item calibrations are stable within –1 logit to +1 logit [101]. It is also worth noting that this estimate is conservative because repeated measurements of adherence will provide additional data for evaluating the psychometric performance of the proposed instruments. For the proposed mixed-effects regression models, the sample of 48 families is sufficient for accurate estimates of the focal model parameters, in particular fixed-effects estimates for between-group differences and change over time [102]. Although variance components could be prone to bias, this information is less important for planning the subsequent larger trial as the power estimates can straightforwardly penalize for a range of nesting effects.

For the qualitative interviews with payers and providers of recovery support services, the estimated 10-participant sample size falls within the parameters of 6 to 12 interviews to determine saturation and variability [103]. The credibility of the results will be promoted by ensuring that the investigators have the required knowledge and skills to perform their roles of interviewing and coding, requiring the interviewer to maintain field notes that will be stored with the data, including a peer review process of coding, and using a semistructured interview guide that includes prompts that allow for elaboration of answers and the chance to ask for more information as needed, allowing for both focus and adjustability during interviews [104]. Transferability of the qualitative results will be promoted by using purposeful sampling and reaching data saturation, when no new codes are identified in the transcripts and the research team agrees that theoretical saturation has been reached through the discussion of coding and identifying any variation in key concepts [16].

## Results

We are currently engaging recovery community organizations as potential recruitment sites for emerging adult and parent participants, as well as for participating peer workers to take the vocational or educational toolkit training and deliver *Launch* services. We have also engaged a parent coach and initiated training. This project was funded (grant R34DA057639) in August 2023 and is currently expected to end in September 2025. We anticipate publication of the results of this study in late 2026. Participants are expected to begin enrolling in June 2024.

## Discussion

### Expected Findings

We anticipate that the *Launch* research protocol and both services (virtual CM-EA parent coaching and peer workers specially trained in vocational or educational goal setting) will be reported as acceptable, appropriate, and feasible and that feedback for improving the research and service models will be qualitatively provided, which will be incorporated into a future larger-scale study, leading to further reports of acceptability, appropriateness, and feasibility in follow-up projects. Results from this project will be disseminated via peer-reviewed manuscripts and presentations at professional conferences as well as to interested research participants. In addition, data from this study will be stored in the Helping to End Addiction Long-Term Data Repository after the completion of analyses as required by the funding agency for further investigation.

A strength of *Launch* is that it is explicitly tailored for the state of recovery capital with which emerging adults present, and this pilot allows for a preliminary exploration of *Launch*’s acceptability for targeting emerging adults’ recovery capital domains [14,29,105-108]. *Launch* leverages existing resources in rural areas—parents and peer workers—and examines whether CM-EA can be delivered virtually to parents and by paraprofessional coaches versus clinicians who are in short supply in rural communities [109]. Formative research on CM has involved delivery by paraprofessionals, and this approach has been deemed both feasible and efficacious [65]. The use of peer workers had a similar motivation as they are also paraprofessionals and a local workforce found in most regions of the United States [110].

